
### Methods and statistical analysis

Statistical analysis will be completed based on the RE-AIM (Reach, Effectiveness, Adoption, Implementation, Maintenance) framework based on methods as outlined below.

### Reach

Methods determining EPICS’s reach included: establishing inclusion criteria and documenting exclusions, participation rates, dropouts and representativeness; assessing size and characteristics of NBLIC community coalitions and church, clinical and community settings to determine barriers to participation (*e.g.*, infrastructure, time, priorities, etc.); assessing the proportion of eligible participants (African American, age 50 to 74, either gender) per setting consenting participation; documenting the number of community coalitions by characteristics; description of settings (total number of eligible participants); and estimating the number of eligible individuals and completers of EPICS sessions per setting. Proportion of eligible community coalitions and settings aware of EPICS will be calculated and two-group *t* tests and chi-square tests to compare those aware versus not aware will be completed. Analysis of variance will compare the degree of change in EPICS awareness among leaders of community coalitions and settings and the increase in post intervention CRC screening knowledge scores will be determined using a paired *t* test.

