**Methods/design:**

In this study, investigators will recruit 20 community coalitions and 7,200 African-Americans age 50 to 74 to test passive and active approaches to disseminating the Educational Program to Increase Colorectal Cancer Screening (EPICS); to measure the extent to which EPICS is accepted and the fidelity of implementation in various settings and to estimate the potential translatability and public health impact of EPICS. This four-arm cluster randomized trial compares the following implementation strategies: passive arms, (web access to facilitator training materials and toolkits without technical assistance (TA) and (web access, but with technical assistance (TA); active arms, (in-person access to facilitator training materials and toolkits without TA and (in-person access with TA). Primary outcome measures are the reach (the proportion of representative community coalitions and individuals participating) and efficacy (post-intervention changes in CRC screening rates). Secondary outcomes include adoption (percentage of community coalitions implementing the EPICS sessions) and implementation (quality and consistency of the intervention delivery). The extent to which community coalitions continue to implement EPICS post-implementation (maintenance) will also be measured. Cost-effectiveness analysis will be conducted.

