### Goals and aims

The overall goals of this research are to identify the most efficacious approach to disseminating EPICS and to identify the factors associated with its effectiveness.

Key aims are to:

1. Test passive and active approaches to disseminating EPICS.

2. Measure the extent to which EPICS is accepted by community coalitions and the fidelity of implementation in various settings.

3. Estimate the potential for translation and the public health impact of EPICS.

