### Community coalitions

The community coalitions that will serve as clusters in the EPICS cRCT are part of the National Black Leadership Initiative on Cancer (NBLIC), a network that was founded in 1987 and have primarily engaged in community education efforts; this history has been described elsewhere [11]. The coalitions include individuals from academia, business, health care, non-profit organizations, and other community stakeholders. Twenty of the 33 NBLIC community coalitions will be randomized as clusters in the EPICS cRCT. In developing this project, we executed Memoranda of Understanding (MOU) between the coalitions and Morehouse School of Medicine; recruited research sites and surveyed the community coalitions’ organizational characteristics.

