### Sample size calculation

We intend to enroll 7,200 individuals in this study, with 1,800 enrolled in each study arm. This sample size is based on 20 NBLIC community coalitions randomized to four study arms (WA, WA + TA, IP, IP + TA). There will also be three settings (church, clinic, and community site) per coalition. Each community coalition will have 30 groups of individuals completing three consecutive EPICS sessions, recruiting 15 individuals per setting with an expected 25% dropout rate; thus, we anticipate that 12 of these individuals will complete all three sessions. For the EPICS cRCT, there will be (30 groups of three sessions) × (12 individuals completing all three sessions) × (20 NBLIC community coalitions) = 7,200 individuals. Based on data from a previously published study, we calculated intracluster correlation coefficient (ICC) to equal 0.0911 (9.1%) [6]. The effective sample size (ESS) was 5,645, which still has high power (>99%) with design effect of 1.2754.

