### Primary outcome measures

The primary outcome for the EPICS cRCT focuses on the Reach and Effectiveness components of the RE-AIM (Reach, Effectiveness, Approach, Implementation, Maintenance) model. Reach refers to the proportion of representative eligible organizations, settings, and individuals participating in the intervention. To determine EPICS Reach, we will examine two dimensions of this concept, estimated based on the following calculation [24]:

Number of participants in

$$\text{Estimate}\;\text{of}\;\text{REACH}=\frac{\text{the}\;\text{target}\;\text{population}\;\text{who}\;\text{receive}\;\text{the}\;\text{three}\;\text{EPICS}\;\text{sessions}\;\times \;100}{\text{Number}\;\text{of}\;\text{eligible}\;\text{participants}\;\text{in}\;\text{the}\;\text{target}\;\text{settings}}$$

In the RE-AIM framework, effectiveness is the impact of the intervention on desired outcomes. For the EPICS cRCT, CRC screening adherence will be based on baseline community CRC screening rates from the Centers for Disease Control and Prevention’s (CDC) Behavioral Risk Factor Surveillance System (BRFSS), post intervention participant self-reported FOBT, flexible sigmoidoscopy and/or colonoscopy, and changes in facilitators’ CRC knowledge, attitudes, and beliefs. Adherence to CRC screening on a total population basis is calculated as:

Number of participants

$$\text{Adherence}\;\text{to}\;\text{CRC}\;\text{screening}=\frac{\text{adherent}\;\text{to}\;\text{CRC}\;\text{screening}\;\text{in}\;\text{the}\;\text{population}}{\text{Estimated}\;\text{target}\;\text{population}\;\text{by}\;\text{setting}}$$

In alignment with Glasgow’s RE-AIM definition, our estimate of effectiveness will be determined using the following formula [24]:

Number of participants in the sample of the target population

$$\text{Estimate}\;\text{of}\;\text{Effectiveness}=\frac{\text{who}\;\text{were}\;\text{Reached}\;\text{and}\;\text{adherent}\;\text{to}\;\text{CRC}\;\text{screening}}{\text{Number}\;\text{of}\;\text{participants}\;\text{in}\;\text{the}\;\text{target}\;\text{population}\;\text{who}\;\text{were}\;\text{reached}}$$

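### The tests stated for the co-primary outcome Reach do not compare the Reach proportion between the randomised arms

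*Protocol article*

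**What the plan says.** The Abstract states: "Primary outcome measures are the reach (the proportion of representative community coalitions and individuals participating) and efficacy". Under Primary outcome measures, "Reach refers to the proportion of representative eligible organizations, settings, and individuals participating in the intervention". The formula that follows divides the number of people in the target population who receive the three sessions by the number of eligible people in the target settings, times 100.

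The first aim is to "Test passive and active approaches to disseminating EPICS", and the units allocated are "20 NBLIC community coalitions randomized to four study arms".

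The section Methods and statistical analysis opens by saying that analysis will follow the methods it then sets out under the RE-AIM headings. Under Reach, it first lists counts and proportions to be documented or estimated, including eligible people and completers per setting. It then names three sets of tests:

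- The first set splits coalitions and settings by awareness of EPICS. It has t tests for two groups, and the article also says that "chi-square tests to compare those aware versus not aware will be completed".
- The second concerns leaders and is worded as follows: "Analysis of variance will compare the degree of change in EPICS awareness among leaders of community coalitions and settings".
- The third is a t test on paired knowledge scores, which the article introduces thus: "the increase in post intervention CRC screening knowledge scores will be determined using a paired".

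Elsewhere, hypothesis one (H1) predicts greater enrolment with active than with passive dissemination. The Power analysis assumes a two-sided two-group chi-square test with 1,800 per arm, comparing each of the other three arms with web access alone.

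**The concern.** The trial randomises coalitions to four dissemination strategies in order to learn which works better. For Reach, that means asking whether the proportion of eligible people who complete the sessions differs between arms. The Reach section names its tests, and none of them asks this. Awareness of EPICS is not a randomised factor, a change in leaders' awareness is not Reach, and a paired test of knowledge is a within-person contrast.

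At stake is one of the two primary outcomes. An analyst who follows the section would report awareness and knowledge results and no arm comparison of Reach. One who notices the gap would have to choose the outcome, the contrast and the handling of clustering later, possibly with the data in hand.

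**Working it through.** **1. The stated tests against the defined outcome**

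| Stated test (Reach section) | Outcome | Groups compared | Reach proportion by arm? |
|---|---|---|---|
| t and chi-square tests | none named | aware and unaware coalitions and settings | no |
| Analysis of variance | change in awareness | leaders of coalitions and settings; arm not named | no |
| Paired t test | knowledge score | before and after, same people | no |

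The next section, Effectiveness, does name a comparison of screening rates between passive and active approaches. An arm comparison therefore fits the article's level of detail, and Reach has no counterpart to it.

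**2. Does the H1 test fill the gap?**

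*Outcome.* H1 is about enrolment, while Reach counts completers of three sessions. Sample size calculation separates the two: 15 recruited and 12 completing per group. Over the trial:

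- recruited: 30 × 15 × 20 = 9,000;
- completing: 30 × 12 × 20 = 7,200, which reproduces the article's total.

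Two arms with equal enrolment and unequal dropout would look the same on H1 and differ on Reach.

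*Denominator.* 7,200 / 4 = 1,800 per arm, so by this derivation 1,800 is the planned number of completers. That is the numerator of Reach, not the eligible population by which Reach is divided.

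*Contrast.* H1 is active versus passive. The Power analysis compares three arms with web access alone, and one of those three (web plus TA) is itself a passive arm.

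*Clustering.* The Power analysis enters 1,800 per arm as it stands. The design effect of 1.2754 given in the Sample size calculation (7,200 / 1.2754 = 5,645, reproduced) is not applied there. As an illustration, take the stated ICC of 0.0911 to hold at coalition level (an assumption) with 7,200 / 20 = 360 people per coalition:

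- design effect = 1 + (360 − 1) × 0.0911 = 33.7;
- 1,800 / 33.7 ≈ 53 effective people per arm.

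An individual-level chi-square is therefore not a safe default for a Reach comparison.

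**3. The one stated figure for a between-arm comparison: power above 99% for H1**

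Check: n = 1,800 per arm, two-sided alpha 0.05, power = Φ{(|p1 − p0| − 1.96 √[2p̄(1 − p̄)/n]) / √[(p0(1 − p0) + p1(1 − p1))/n]}, with p̄ the mean of p0 and p1. The web-only proportion p0 is 5%, 10% or 20%, as in the article. The wording of the 25%, 33% and 50% greater enrolment allows three readings:

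- as added percentage points: above 99% in all nine cells;
- as the arms' own proportions: above 99% in eight of nine; 20% versus 25% gives 94.9%;
- as relative increases: 37.0%, 56.1% and 87.3% from 5%; 66.1%, 87.0% and 99.5% from 10%; 94.9%, 99.7% and about 100% from 20%.

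The figure reproduces in full on one reading only, so it is ambiguous rather than shown to be wrong. The present point does not depend on it, since the figure concerns enrolment.

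**The case against.** The strongest reply has three parts.

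First, the article does contain a between-arm comparison. H1 with its chi-square is plainly the hypothesis closest to Reach, which the article describes as the proportion participating, and the cost-effectiveness section compares outcomes across all four strategies. This stands in part. A reader might infer that Reach has no randomised comparison anywhere, and that would go too far. But the H1 test is for another quantity and is stated only for power. The cost-effectiveness comparison takes screening adherence as its measure of effect.

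Second, the tests of aware against unaware units name no outcome. They may only check how representative those units are, as the Adoption section does for adopters and non-adopters. This stands. It follows that a reader cannot conclude that the stated test would find a difference in Reach even if all strategies performed equally: the article never says that Reach is the variable tested, and it treats awareness as something that can change. Nor can one conclude that the randomised coalitions contain no unaware group. The article says "we executed Memoranda of Understanding (MOU) between the coalitions" and the school, but it does not define awareness, say when it is measured, or limit the comparison to the 20 randomised of the 33 network coalitions. If the tests compare characteristics only, they are not tests of Reach, and the gap remains.

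Third, a condensed article may leave tests to an analysis plan that is not shown. That would answer a silent section. This section is not silent: it selects tests for a primary outcome, and those it selects leave out the randomised contrast.

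**Conclusion.** The concern holds in a bounded form. The section that fixes the Reach analysis names tests of other contrasts and omits a comparison of the defined Reach proportion between randomised arms. The related H1 test does not close the gap, because it differs in outcome and denominator, ignores allocation by coalition, and is not carried into the analysis section.

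No numerical bias or error rate follows from the documents, and none is claimed. The consequence is that a primary outcome lacks a prespecified analysis matching the trial's first aim. The conclusion rests on reading the Reach section as the statement of tests for that outcome, as the opening of Methods and statistical analysis presents it. It should be corrected before outcome data are examined.

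**What to change.** In the Reach section, state along these lines: the primary analysis of Reach compares the proportion defined under Primary outcome measures between randomised arms, active versus passive as in H1. It uses one value per coalition, or a model that allows for clustering by coalition, and randomised coalitions that deliver no sessions count as 0. List as further comparisons either the contrasts of each arm with web access alone from the Power analysis or the contrast of TA with no TA. Say how H1 enrolment relates to Reach. Keep awareness as a descriptive process or representativeness measure, not as the analysis of Reach.

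The cost is wording only, because the section already plans to estimate eligible people and completers per setting. The downside is that precision becomes visibly limited. With 20 coalitions split equally (an assumption), a comparison of coalition means has 10 + 10 − 2 = 18 degrees of freedom for active versus passive, and 5 + 5 − 2 = 8 for one arm against web access alone.

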### Power analysis

Power calculations were performed to further justify our proposed sample size. All of these assume a sample size of 1,800 per study arm, a significance level of 5% (*i.e.* alpha = 0.05), and a two-sided two-group chi-square test of proportions. Calculations were performed using nQuery Advisor, version 7. These are performed for hypothesis one (H1) and hypothesis three (H3); hypothesis two (H2) is qualitative, so power calculations do not apply. For H1, we anticipate that there will be 25%, 33%, and 50% greater participant enrollment with the Web + TA arm, IP arm, and IP + TA arm, respectively, when compared to the passive web-based-only arm (based on our prior experience with community coalition based studies). Comparisons of any of these proportions to any proportion that is obtained for the passive web-based arm (for example, 5%, 10%, or 20%) will result in greater than 99% power to detect differences in the proportions as being statistically significant. For H3, we can obtain estimates of cancer knowledge change over time (pre-intervention to post-intervention percentages with the correct response) for a small group education cohort and a control cohort from Blumenthal, Smith *et al.*[6]. These estimates include changes of 34.8 (71-36) and 15.5 (55.2-39) for a CRC perceived risk question, and 22.9 (92.9–70) and 13.1 (88.5–75.for a CRC screening question. Assuming that we observe similar changes in our study participants for active and passive arms, we will have greater than 99% power to detect differences in the proportions as being statistically significant.

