### Effectiveness

To determine effectiveness, investigators will: compare CRC screening rates of passive and active dissemination approaches by setting; examine baseline/post CRC screening rates (community coalition catchment area) and compare baseline/post CRC knowledge attitudes; and beliefs of facilitators (training) and participants (EPICS sessions). Effect size will be computed by subtracting mean CRC screening rates in communities aware and not aware of EPICS divided by the pooled standard deviation of CRC screening rates. The proportion of community coalitions and settings aware of EPICS (effectiveness-organizational level) and that deliver it (adoption) will also be determined.

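### The sample size for H3 rests on an active-versus-passive comparison of knowledge change, but the analysis sections name only a before/after comparison for knowledge

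*Protocol article*

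**What the plan says.** **Analysis sections.** Under Reach, the protocol article states that "the increase in post intervention CRC screening knowledge scores will be determined using a paired" t test. Under Effectiveness, investigators will "compare baseline/post CRC knowledge attitudes; and beliefs of facilitators (training) and participants (EPICS sessions"). Neither sentence mentions study arm. The same sentence under Effectiveness does compare passive with active approaches, but for screening rates.

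**Power analysis.** The calculations use "a significance level of 5% (*i.e.* alpha = 0.05), and a two-sided two-group chi-square test of proportions", and "All of these assume a sample size of 1,800 per study arm". For H3 the inputs are changes in the percentage answering correctly "for a small group education cohort and a control cohort" of the earlier trial. On perceived risk the article writes: "These estimates include changes of 34.8 (71-36) and 15.5 (55.2-39) for a CRC perceived risk question". The corresponding figures on screening knowledge are given as "and 22.9 (92.9–70) and 13.1 (88.5–75.for a CRC screening question". The section then concludes: "Assuming that we observe similar changes in our study participants for active and passive arms, we will have greater than 99% power" to detect the difference. So the contrast sized is active versus passive.

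**Context.** The Toolkit section (EPICS Curriculum item) has participants in every arm complete the three sessions. Aim 1, under Goals and aims, is to test passive and active dissemination. The Background reports that knowledge did not increase significantly in the earlier trial's control cohort. H3 as worded concerns a correlation between knowledge and perceived risk, so it does not supply the arm contrast either.

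**The concern.** A paired test of post against pre estimates one quantity, the mean change. With no untreated group, that quantity contains whatever the sessions did plus everything that moves all arms alike, such as repeat testing, outside publicity, or better retention of motivated people. It carries no information on the randomised factors, which are in-person versus web delivery and technical assistance versus none.

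The plan therefore justifies part of its sample by a question that its analysis sections do not ask, and asks one that it did not size. Followed as written, it is likely to report a significant knowledge gain that says nothing about aim 1, while the contrast that could bear on aim 1 goes unreported for knowledge.

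**Working it through.** **1. Reproduce the plan's power for H3.** Enter the changes as two proportions, as the stated chi-square test does, with n = 1,800 per arm and two-sided alpha 0.05.

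Formula: z = [d − 1.96·√(2·p̄(1−p̄)/n)] / √[(p1(1−p1) + p2(1−p2))/n]

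- Perceived risk, 34.8% v 15.5%: d = 0.193, p̄ = 0.2515. Standard errors are 0.01446 (null) and 0.01410 (alternative). z = (0.193 − 0.0283)/0.01410 = 11.7; power above 99.99%.
- Screening item, 22.9% v 13.1%: d = 0.098, p̄ = 0.180. Standard errors are 0.01281 and 0.01270. z = (0.098 − 0.0251)/0.01270 = 5.7; power above 99.99%.

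The stated figure of more than 99% is reproduced, for a between-arm test.

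**2. Set the two tests side by side.**

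| | Power analysis | Reach and Effectiveness |
|---|---|---|
| Comparison | active v passive arms | post v pre |
| Test | two-group chi-square | paired t (Reach); none named (Effectiveness) |
| Arm term | yes | none stated |

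**3. How large can the part unrelated to EPICS be?** The earlier control cohort's change, as a share of the education cohort's change:

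- Perceived risk: 15.5/34.8 = 45%
- Screening item: 13.1/22.9 = 57%

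These are point estimates from two items.

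**4. What would the paired test do with such a rise?** Suppose EPICS adds nothing and all 7,200 participants show only the control cohort's change. Take each item as correct/incorrect, so z = d/(sd/√n), with sd = √(discordance − d²) and √7,200 = 84.85.

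The pre values are partly cut off in the text available, so they are inferred as 55.2 − 15.5 = 39.7 and 88.5 − 13.1 = 75.4. Discordance is not given. The range runs from its minimum (every change upward, discordance = d) to independence of pre and post.

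- 15.5 points, minimum: sd = √(0.155 − 0.0240) = 0.362; z = 36.3
- 15.5 points, independence: discordance = 0.397×0.448 + 0.603×0.552 = 0.511; sd = 0.698; z = 18.9
- 13.1 points, minimum: sd = √(0.131 − 0.0172) = 0.337; z = 32.9
- 13.1 points, independence: discordance = 0.754×0.115 + 0.246×0.885 = 0.304; sd = 0.536; z = 20.7

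**5. Does this depend on ignoring clustering?** As an assumption, apply the plan's ICC of 0.0911 to 7,200/20 = 360 people per coalition. The design effect is 1 + 359×0.0911 = 33.7 and the effective n is 7,200/33.7 = 214. The z values become 3.2 to 6.3 (15.5 points) and 3.6 to 5.7 (13.1 points), still above 1.96. A cluster-adjusted paired test asks the same question and gets the same kind of answer.

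**6. What would an arm contrast do?** If active and passive arms rise equally, the expected difference is zero and the shared rise cancels. What remains is the effect of dissemination mode.

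**The case against.** The case on the other side is substantial, and several parts of it stand.

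- A reader might infer that the plan contains no between-arm contrast for knowledge. It does contain one, in the Power analysis section; it is the analysis sections that do not carry it.
- A reader might infer that the paired test pools all arms and that the gain will be credited to EPICS. Neither is written. The Reach sentence is silent on arms and makes no causal claim. The Effectiveness section places the baseline/post comparison under determining effectiveness, but does not say how a change will be attributed.
- A paired t test is a valid test of whether knowledge rose. The large z values above show power to detect a real rise; they are not an inflated type I error and should not be set against the 5% level.
- The 15.5 and 13.1 points come from a small cohort in a trial that randomised 369 people in all, and the Background reports no significant rise there. They illustrate the size of a possible shared rise but do not establish it. The plan's outcome is also a score, not these single items.
- Participant knowledge is not listed as a primary or secondary outcome, and H1 and the screening-rate comparison address aim 1 by other routes. Only facilitators' knowledge appears under Primary outcome measures.
- A separate analysis plan could name the arm contrast. But the article does name a method for knowledge, and it differs from the one used to justify the sample. Further detail elsewhere would not make these two sections agree.

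**Conclusion.** The point holds as a mismatch between the powered test and the stated test. The H3 power figure is correct on its own inputs, but it belongs to an active-versus-passive comparison, while Reach and Effectiveness specify only change over time for knowledge. Since every arm receives EPICS, that change cannot rank the dissemination strategies.

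The consequence is sizeable if a shared rise like the earlier control cohort's occurs: at 7,200 people it would give a paired z of 19 to 36 (15.5 points) or 21 to 33 (13.1 points) with no contribution from EPICS. This rests on the inferred pre values, on treating the items as binary, and on the stated range of discordance.

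One might go further and say that a better analysis would isolate the effect of EPICS. The design does not allow that, because no arm goes without the sessions. Whether clustering erodes the more than 99% power is a separate question and forms no part of this conclusion. Because knowledge is mostly a supporting measure, the mismatch should be corrected but does not threaten the primary comparison.

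**What to change.** In the Reach and Effectiveness sections, name as the inferential test for participant knowledge, and for facilitator knowledge, a comparison between arms of the post-intervention score adjusted for the pre-intervention score. Include terms for in-person versus web and for technical assistance versus none, with coalition as the cluster. Facilitators belong here because the mode of their training is what is randomised.

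Report the paired pre/post change by arm as descriptive only. State that the arm contrast estimates the effect of dissemination mode and not of EPICS against no EPICS. Align the H3 paragraph of the Power analysis section with the test so named.

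The cost is wording: pre and post measurements and arm are already to be recorded. The result will be less favourable than a near-certain pre/post rise. The facilitator contrast will be the less precise of the two: with at least five members plus a leader per coalition, the planned minimum is 20 × 6 = 120 people.

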**Figure 1 F1:**
[figure not shown]
CONSORT flow diagram for EPICS cRCT.

Randomization at the organizational (community coalition) level has been chosen because this will minimize contamination that may occur if individual participants are randomized. In utilizing cluster randomization, we will focus on community coalitions as the cluster for all study arms, with individuals within their target settings as the secondary unit. We will ensure balance in all four study arms by ordering them into groups based on the total number participating. A computer program generating random numbers between 1 and *n* will be used to assign community coalitions to one of four conditions: web access (WA) to facilitator training materials and toolkits without technical assistance (TA); the same as 1, but with technical assistance (TA); in-person access (IP) to facilitator training materials and toolkits without TA; and in-person access to facilitator training materials and toolkits with TA. Our multilevel approach (*e.g.*, cluster, setting, and individual) promotes widespread dissemination [13]. Community coalitions will be allocated to one of the four arms and informed consent will be obtained from community coalition members and from individual participants.

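### The knowledge increase is tested with a paired t test that makes no stated allowance for clustering, although participants are taught in groups within 20 randomised coalitions

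*Protocol article*

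**What the plan says.** The Reach section of the statistical methods states that "the increase in post intervention CRC screening knowledge scores will be determined using a paired" *t* test. It does not say whose scores these are, and it names no cluster term, robust variance or cluster-level summary.

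The rest of the article describes clustered data:

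- In Trial design, the text after Figure 1 says that "we will focus on community coalitions as the cluster for all study arms".
- In the Sample size calculation, "Each community coalition will have 30 groups of individuals completing three consecutive EPICS sessions", "recruiting 15 individuals per setting with an expected 25% dropout rate", and 12 are taken to complete. That gives 360 completers per coalition and 7,200 in all.
- The same section gives an ICC of 0.0911, a design effect of 1.2754 and an effective sample size of 5,645. It does not say which outcome or which level of clustering the ICC describes.
- Under Primary outcome measures, a GEE with robust inference is specified, but for screening adherence only.

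On whose knowledge is measured, the Effectiveness section plans a before-and-after comparison of the knowledge, attitudes and "beliefs of facilitators (training) and participants (EPICS sessions"). The Power analysis takes its knowledge changes from participants of the earlier trial.

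**The concern.** A paired t test handles the correlation between one person's two scores. It still treats each person's change as independent of everyone else's. People who sit in the same small group, taught by the same facilitators, are likely to gain by similar amounts, and so are people served by the same coalition, because each coalition supplies its own facilitators. Pairing removes stable differences in level between people and coalitions. It does not remove gain that is shared.

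If change is positively correlated within groups or coalitions, the planned standard error is too small, the confidence interval is too narrow and the p-value overstates the evidence. This is not a detail left for an analysis plan: the article fixes a test, and as an individual-level test it conflicts with the way the same article treats its other individual-level outcome.

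**Working it through.** **Inputs.** From the Sample size calculation: 20 coalitions, 30 groups per coalition, 15 recruited and 12 completing per group, ICC 0.0911. From the Toolkit section: at least five facilitators plus a leader per coalition, so about 6. From the Power analysis: two-sided test, alpha 0.05.

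**Formulas**, for cluster size m:

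- Design effect: DE = 1 + (m − 1) × ICC
- Understatement of the standard error: √DE
- Real error of a nominal 5% test: 2 × [1 − Φ(1.96/√DE)]. This applies only if the true mean change is zero.

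**The plan's own figure.** 7,200 / 1.2754 = 5,645, so the division reproduces. The design effect does not. At ICC 0.0911 the formula gives 2.002 for m = 12, 2.275 for m = 15 and 33.70 for m = 360. The printed value equals (15 − 1) × 0.0911 = 1.2754 exactly, so the leading 1 appears to have been left out. This shows the level at which the plan uses its ICC: the session group, not the coalition. The slip needs its own correction. Even with 1.2754 taken as printed, the understatement is √1.2754 = 1.13-fold and the real error about 8%.

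**Session-group level, ICC 0.0911, assuming it applies to change scores**

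| m | DE | SE understated | Real error |
|---|---|---|---|
| 12 | 1 + 11 × 0.0911 = 2.002 | 1.41-fold | 17% |
| 15 | 1 + 14 × 0.0911 = 2.275 | 1.51-fold | 19% |

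**Coalition level, m = 360; the article gives no ICC of change at this level, so a range is assumed**

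| ICC of change | DE | SE understated | Real error |
|---|---|---|---|
| 0 | 1.00 | none | 5% |
| 0.001 | 1.359 | 1.17-fold | 9% |
| 0.01 | 4.59 | 2.14-fold | 36% |
| 0.0911 | 33.70 | 5.81-fold | 74% |

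**If facilitators were meant**, m = 6: DE = 1 + 5 × 0.0911 = 1.456, understatement 1.21-fold, real error about 10%.

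**Simulation.** With 20 coalitions of 360 change scores and no true change (4,000 runs), the individual-level paired test rejected in 9.5%, 36.4% and 74.4% of runs at ICC 0.001, 0.01 and 0.0911. A t test on the 20 coalition means rejected in 5.1% to 5.2%.

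**Interval width.** The planned 95% half-width is 1.96/√7,200 = 0.023 SD of change. With coalition means (19 df, critical value 2.093) it is 2.093 × √(4.59/7,200) = 0.053 SD at ICC 0.01 and 2.093 × √(33.70/7,200) = 0.143 SD at 0.0911.

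**Would the conclusion change?** Probably not for gains like those cited in the Power analysis. With an assumed SD of change of 0.71 and the worst case in the table, the standard error is 0.71 × √(33.70/7,200) ≈ 0.048. The small-group education gains of 22.9 and 34.8 points then give t of about 4.7 and 7.2. The smallest change cited, 13.1 points in the control cohort, gives about 2.7. All exceed 2.093.

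**The case against.** Four points can be made for the plan.

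1. *The population and unit are not stated.* The nearest group named in the sentence is the leaders of coalitions and settings, and facilitators are also measured before and after training. A paired t test on coalition means would be valid, and the words do not exclude it. This stands in part. Participants remain the likelier reading, because the scores are described as post-intervention and the Effectiveness and Power analysis sections both deal with participant knowledge. Nothing in the text points to coalition means.

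2. *The size is uncertain.* A reader might infer that the plan's own ICC makes the standard error 5.8 times too small, with a real error of 74%. The documents do not support that. The article gives neither the outcome nor the level of the ICC, and its source, as the Background describes it, was a trial in one metropolitan area developed with one coalition. The plan's arithmetic uses the ICC at group size. Pairing also cancels stable coalition differences, so the ICC of change may be lower. This stands in full.

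3. *The test is not meant to compare arms.* A reader might infer that, by pooling the arms, it fails the trial's main question. That does not follow. It is one before-and-after item under Reach, and the Power analysis already contemplates a comparison of knowledge change between active and passive arms.

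4. *The consequence is limited.* Large gains would probably stay significant, and knowledge is neither a primary nor a named secondary outcome. This stands, and it limits how much weight the point deserves.

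**Conclusion.** The point holds in a limited form. As written, the article names a paired t test for clustered data with no allowance for clustering, and the only cluster-robust method it describes is reserved for screening adherence.

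The best-supported size is an understatement of about 1.4- to 1.5-fold. It rests on two assumptions: that the scores are the participants', and that an ICC of 0.0911 applies to their changes at session-group level. Any correlation of change at coalition level would add to this, by an amount the documents do not fix. Only an ICC of change close to zero at both levels would remove the problem, and the article gives no reason to expect that. If facilitators were meant, the effect is small, about 1.2-fold.

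The damage is to the interval and the p-value of an outcome that is not primary. It should be corrected, but it does not threaten the trial's main conclusions.

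**What to change.** State whose knowledge scores are analysed. Replace the individual-level paired t test with one of these:

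- a t test on the 20 coalition mean changes (19 df); or
- a mixed model or GEE on individual change, clustered by coalition, with a small-sample correction because there are only 20 clusters.

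Clustering at coalition level also covers the session groups nested within it. Reporting change by arm from the same model is an optional addition.

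This changes the analysis wording only and needs no new data. The downside is a wider interval: under the assumptions above, a half-width of 0.053 SD at a coalition-level ICC of 0.01, against 0.023 SD as planned.
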